**Methods and analysis:**

A prospective, multi-center, assessor-blinded, Phase 2 randomized controlled trial with a superiority framework. Sixty-two stroke patients will be randomized in two groups with a 1:1 allocation ratio, stratified based on arm paresis severity (Fugl-Meyer Assessment—Upper Extremity subscale <32 and ≥32). The experimental group receives a wrist-worn activity tracking device providing multimodal feedback on daily arm use for 6 weeks. Controls wear an identical device providing no feedback. *Sample size*: 31 participants per group, based on a difference of 0.75±1.00 points on the Motor Activity Log—14 Item Version, Amount of Use subscale (MAL—14 AOU), 80% power, two-sided alpha of 0.05, and a 10% attrition rate. *Outcomes*: primary outcome is the change in patient-reported amount of daily life upper limb use (MAL—14 AOU) from baseline to post-intervention. Secondary outcomes are change in upper limb motor function, upper limb capacity, global disability, patient-reported quality of daily life upper limb use, and quality of life from baseline to post-intervention and 6-week follow-up, as well as compliance, activity counts, and safety.

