
### Study Aim

The primary aim of this study is to determine the post-intervention and long-term effects of wearing a wrist-worn, commercially available tracking device that provides multimodal feedback for 6 weeks on patient-reported amount of paretic upper limb use in daily life in hemiparetic subjects beyond 3 months after stroke, when compared with a control group receiving an identical looking device providing no feedback. The secondary aims are to examine the compliance to use the device, and explore the effect on motor function of the paretic upper limb, upper limb capacity, patient-reported quality of paretic upper limb use in daily life, global disability, health-related quality of life, and during the 6-week intervention, the compliance and activity counts of the paretic and non-paretic upper limb. As a measure of safety, the incidence and severity of side effects related to the long-time wrist-worn feedback intervention during the study period will be investigated. Furthermore, the Minimal Clinical Important Difference (MCID) of the Amount of Use (AOU) subscale of the Motor Activity Log—14 Item Version (MAL—14) will be established.

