### Statistical Analysis

Patient demographics and baseline data will be analyzed by trial arm using summary descriptive statistics. Baseline differences between groups will be tested by the independent-samples *t*-test for parametric data, Pearson’s χ^2^ test for categorical data, and the Mann–Whitney *U* test for non-parametric data.

Differences in change scores (T0–T1) between groups will be analyzed for the primary outcome (MAL—14 AOU) and secondary outcomes (MAL—14 QOM, FMA—UE, ARAT, EQ-5D-5L, mRS, and Quantitative Sensor Data). In addition, change will be monitored in the follow-up assessments (T1–T2). An analysis of covariance will be applied, with the baseline value of the measure of interest as a covariate. Compliance to using the devices during the 6-week intervention period and safety data will be presented by trial arm with descriptive statistics and compared between groups by the independent-samples *t*-test, Pearson’s χ^2^ test, or Mann–Whitney *U* test, depending on the nature of the data distribution. In a secondary analysis, compliance to wearing the trackers—based on the Quantitative Sensor Data—will be added as a covariate for analysis of the primary outcome MAL-14 AOU.

All randomized subjects will be included in the analyses according to the intention-to-treat approach. Missing data will be imputed. In addition, differences in baseline characteristics of patients who did and did not dropout will be formally tested. A *p*-value of <0.05 will be considered to be statistically significant. The analyses will be performed in IBM SPSS Statistics 23.

Furthermore, the compliance to the intervention will be presented with descriptive statistics. The MCID will be calculated based on the MAL—14 AOU and GRPC scores, analogue to previous work by Lang et al. (37).

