The applied tracking and feedback device focuses on the number of times that the patient moves the paretic upper limb in daily life. The MAL—14 AOU as a primary outcome matches this goal, by asking patients to rate how often they have used their paretic upper limb in daily life activities. We hypothesize that the change in MAL—14 AOU from baseline to post-intervention and follow-up will significantly differ between the experimental and control groups, favoring the experimental group. We expect that this difference will be also clinically relevant. This means that the change observed in the experimental group from baseline to post-intervention is at least 0.75 points more when compared with the control group. The latter is especially important, as clinical applicability and acceptability are highly dependent on whether a statistically significant difference is also meaningful for clinical practice. Although this study is not powered for our secondary outcomes, we expect to see relevant differences between groups regarding upper limb capacity (ARAT) and changes in upper limb activity counts as measured by the tracker devices itself during the 6-week intervention. Contrary, we do not expect to find clinically relevant change on motor function of the paretic upper limb (FMA—UE). First of all, because the feedback does not relate to QOM. Second, while patients in the chronic phase usually do not show significant, clinically relevant changes on motor function beyond 3 months post-stroke (44, 45). Furthermore, we do not expect to see a difference between groups regarding safety and compliance to wear the devices.

A positive result of this study will underline the importance of tracking and feedback on daily life upper limb use after stroke. It would provide therapists with a tool to enhance their patients’ real-world upper limb use, without being labor-intensive. Furthermore, the application of a tracking and feedback device could potentially reduce healthcare costs, although that is something that is beyond the scope of the present study.

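### The only follow-up contrast in the analysis section is T1–T2 change, which cannot test the stated hypothesis about change from baseline to follow-up

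*Protocol article*

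**What the plan says.** All references are to the protocol article.

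- **Statistical Analysis**, post-intervention: "Differences in change scores (T0–T1) between groups will be analyzed for the primary outcome" and for the listed secondary outcomes.
- **Statistical Analysis**, follow-up: "In addition, change will be monitored in the follow-up assessments (T1–T2"). No T0–T2 contrast appears in the section.
- **Statistical Analysis**, model: "An analysis of covariance will be applied, with the baseline value of the measure of interest as a covariate". This sentence directly follows the T1–T2 sentence and does not say which contrasts it covers.
- **Discussion**: "We hypothesize that the change in MAL—14 AOU from baseline to post-intervention and follow-up will significantly differ between the experimental and control groups". The Discussion also expects the gain in arm use to hold at follow-up.
- **Abstract, Methods and analysis**: the clinical and patient-reported secondary outcomes are changes "from baseline to post-intervention and 6-week follow-up". For the primary outcome the Abstract names post-intervention only.
- **Study Aim**: "The primary aim of this study is to determine the post-intervention and long-term effects". No contrast is named there.
- **Measures, including Table 1**: the primary endpoint is the T0–T1 change, and MAL-14 AOU is collected at T0, T1 and T2.

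**The concern.** The Discussion commits to a comparison of the groups on change from T0 to T2. The analysis section plans a different quantity for the same visit. T1 is measured after randomisation and after the intervention, so T1–T2 change asks whether the arms move apart or together once the 6-week intervention has ended. It does not ask whether the feedback arm is better off at follow-up.

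The authors' favoured outcome, a benefit that holds, is one in which T1–T2 should show no group difference. A device that never had an effect predicts the same. A report confined to the planned contrasts would therefore not answer the long-term question directly. A non-significant T1–T2 result could also be mistaken for evidence that the benefit lasted.

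**Working it through.** **Inputs from the Sample Size section:** difference 0.75, SD 1.00, two-sided alpha 0.05, power 80%, 28 per group. The documents give no SD for T0–T2 or T1–T2 change and no inter-visit correlation, so the values used for these below are assumptions.

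**1. The plan's own figure.** n = 2 × (1.960 + 0.842)² × 1.00² / 0.75² = 27.9, so 28 per group. This reproduces the plan. Power at 28 per group is 80.1% by normal approximation and 78.7% by the exact t-test.

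**2. What each contrast estimates.** Let δ1 and δ2 be the group effects at T1 and T2. Randomisation makes the expected difference at T0 zero.

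- T0–T1 change: δ1
- T0–T2 change: δ2, the quantity in the Discussion hypothesis
- T1–T2 change: δ2 − δ1

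With full retention, δ2 = δ1 and the T1–T2 difference is 0. With no effect at any time, δ1 = δ2 = 0 and it is again 0.

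**3. Rejection rates.** Here δ1 = 0.75, n = 28 per group, and SD is 1.00 for both contrasts. SE = 1.00 × √(2/28) = 0.267. Normal approximation:

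| Share of benefit kept at T2 | T1–T2 expected difference | T1–T2 rejects | T0–T2 expected difference | T0–T2 rejects |
|---|---|---|---|---|
| 100% | 0 | 5% | 0.75 | 80% |
| 50% | −0.375 | 29% | 0.375 | 29% |
| 0% | −0.75 | 80% | 0 | 5% |

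The exact t-test gives 79% where the table shows 80%, and 28% where it shows 29%. At full retention the T1–T2 rate is the test's own 5% level, whatever the SD.

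**4. Check by simulated ANCOVA.** Settings: 5,000 runs, T0 value as covariate, change SD 1.00, assumed inter-visit correlation 0.5 to 0.8.

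- Full retention: T1–T2 rejects in 4.7% to 5.4% of runs.
- No effect ever: T1–T2 rejects in 4.9% to 5.5% of runs. The contrast cannot tell these two situations apart.
- Full retention, T0–T2 contrast: 82% power at correlation 0.8, 89% at correlation 0.5.

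**5. How weak a null T1–T2 result is as evidence of retention.** Suppose half the benefit is lost (0.375), with 28 per group and the exact t-test:

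| Assumed SD of T1–T2 change | SE | Loss detected | Loss missed |
|---|---|---|---|
| 0.50 | 0.134 | 79% | 21% |
| 0.75 | 0.200 | 45% | 55% |
| 1.00 | 0.267 | 28% | 72% |

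**The case against.** **The follow-up wording may be descriptive.** T0–T1 differences are to be analysed, whereas follow-up change is only to be monitored. On that reading T1–T2 is a reasonable way to track retention, and rejection rates for it do not apply. This is fair, and the text does not settle it. But then the Discussion's significance hypothesis for T0–T2 has no planned test at all, so the mismatch remains.

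**The article condenses a fuller protocol.** True, and silence would be no finding. Here the article is not silent: it names a follow-up contrast, and that contrast differs from the one in its own hypothesis.

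**The baseline covariate for T1–T2 might mean the T1 value.** The model would then adjust for a post-randomisation outcome and still not estimate the T0–T2 effect. In simulation with full retention it gave differences of 0.15 to 0.38 and rejected in 9% to 32% of runs, for correlations from 0.8 down to 0.5.

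**Stronger readings that the documents do not support:**

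- *Aim, Abstract and hypothesis all define the long-term MAL-14 AOU effect as T0–T2.* The Study Aim names no contrast, and the Abstract phrase covers secondary outcomes. For MAL-14 AOU the definition rests on the Discussion sentence alone, which is explicit enough.
- *T1–T2 is null precisely when the benefit is retained.* It is equally null when there was never an effect.
- *A null T1–T2 result will be reported as retention.* No section states such a rule. The expectation that gains hold is only an expectation.
- *The missed-loss figures show T0–T2 to be the more powerful contrast.* With half the benefit lost and SD 1.00 for both, each contrast has about 29% power. The case for T0–T2 is that it matches the hypothesis.

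**Conclusion.** The point holds as a mismatch between the analysis section and the document's own follow-up hypothesis. T1–T2 change cannot test a between-group difference in change from baseline to follow-up. If the T1–T2 look is only descriptive, no such test is planned.

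With 28 per group and 0.75 fully retained, T1–T2 rejects about 5% of the time at any SD. A T0–T2 contrast would have about 79% power, assuming its change SD equals the 1.00 planned for T0–T1. The risk of missing a half loss, 21% to 72%, rests on the assumed T1–T2 SD of 0.5 to 1.00 and on a formal test being made.

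A reader might infer that the trial's main result is compromised. It is not: the primary endpoint is T0–T1, the sample size was set for it, and the T2 data needed for the right contrast are already collected. This should be corrected before analysis, but it concerns a secondary time point.

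**What to change.** In Statistical Analysis, replace the T1–T2 sentence with two statements:

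1. The secondary follow-up analysis is the between-group T0–T2 contrast for MAL-14 AOU and for the secondary outcomes measured at T2. It uses the T2 score or the T0–T2 change in an ANCOVA with the T0 value as covariate, as for T0–T1.
2. T1–T2 change is reported by group as a descriptive estimate, with the group difference and its 95% CI, and no claim of retention is drawn from a p-value.

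T0–T1 remains the only primary contrast. The cost is a sentence or two of analysis text, with no new data, visits or participants. Settling it before the data are analysed also removes a later choice between two follow-up contrasts.

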## Methods and Analysis

### Study Design

The present study is a multi-center, assessor-blinded, Phase 2 randomized controlled trial with a superiority framework, including two parallel study arms. Patients will be informed about the study, including its procedures, and enrolled by a study team member. Randomization will be stratified based on severity of upper limb paresis [Fugl-Meyer Assessment—Upper Extremity subscale (FMA-UE) <32 and ≥32] (23) with a 1:1 allocation ratio. At the time of patient registration in the centralized web-based database (REDCap™), patients will be given a unique study identification number that is linked to a computer-generated randomization assignment using a pre-set list of random numbers. The pre-set list of random numbers was generated based on a seed number (SAS^®^ 9.3) and balanced based on the stratification in blocks of 4. Randomization is performed by a study member not involved in the outcome assessments.

An Emergency Code Break will be available to the investigator. This Code Break should only be opened in emergency situations when the identity of the investigational product must be known by the investigator in order to provide appropriate medical treatment.

This study was approved by the Cantonal Ethics Committee Zurich and Cantonal Ethics Committee Northwest and Central Switzerland (BASEC-number 2017-00948). All subjects will give written informed consent in accordance with the Declaration of Helsinki. The trial is registered at https://clinicaltrials.gov, unique identifier NCT03294187 prior to patient recruitment.

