### Sample Size

A sample size calculation based on a difference between groups in change from baseline to post-intervention in the AOU subscale of the MAL—14 of 0.75 points. With an effect SD of 1.00, a two-sided alpha level set at 0.05, and a power of 80%, 28 subjects per group are required (24). Taking into account an attrition rate of 10%, a total of 62 subjects will be randomized. In case of an attrition rate higher than the expected 10%, post-recruitment for replacement will take place.

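### The primary ANCOVA leaves out the FMA-UE severity stratum used in randomisation, so the test may be mildly conservative if severity predicts change beyond baseline

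*Protocol article*

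**What the plan says.** Study Design in the protocol article: "Randomization will be stratified based on severity of upper limb paresis", with cut-off FMA-UE <32 versus ≥32 and "with a 1:1 allocation ratio". The allocation list was "balanced based on the stratification in blocks of 4". No other stratification factor is named.

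Statistical Analysis, for between-group differences in change on the primary outcome and most secondary outcomes: "An analysis of covariance will be applied, with the baseline value of the measure of interest as a covariate". One further covariate is mentioned. In a secondary analysis, compliance with wearing the trackers "will be added as a covariate for analysis of the primary outcome MAL-14 AOU". The FMA-UE stratum is in neither model.

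Sample Size rests on a "difference between groups in change from baseline to post-intervention in the AOU subscale of the MAL—14 of 0.75 points". It continues: "With an effect SD of 1.00, a two-sided alpha level set at 0.05, and a power of 80%, 28 subjects per group are required". And then: "Taking into account an attrition rate of 10%, a total of 62 subjects will be randomized".

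**The concern.** Stratified blocks hold the two arms close to balance on severity. If severity is related to outcome, that balance lowers the true sampling variance of the treatment difference. A model without the stratum leaves the between-stratum variation in its residual, so its standard error does not reflect the balance that the design bought. Confidence intervals are then wider than they need to be, and the test rejects less often than its nominal level under the null.

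At stake is efficiency in a small trial, with 28 evaluable patients per group against a target power of 80%. Baseline AOU need not absorb all the information on severity. AOU is a patient-reported use score from 0 to 5, while FMA-UE is a motor function score from 0 to 66 built on ratings of performed movements.

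**Working it through.** **Plan's own figure.** Inputs from Sample Size: difference 0.75, SD 1.00, two-sided alpha 0.05, power 80%.

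n per group = 2 × (1.960 + 0.842)² × 1.00² / 0.75² = 2 × 7.85 / 0.5625 = 27.9, so 28. This reproduces. Power at 28 per group is 80.1% by the normal approximation and 78.7% by the noncentral t. For attrition, 28 × 1.10 = 30.8, so 31 per group and 62 in total, as stated. (Dividing 56 by 0.90 gives 63.) Neither stratification nor a covariate enters this calculation.

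**Approximate cost of omitting the stratum.** Let R² be the share of the variance in change, left after baseline AOU, that the stratum explains. The ratio of the model standard error without the stratum to that with it is about 1/√(1 − R²).

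**Simulation check.** 56 evaluable patients, 1:1 allocation in permuted blocks of 4 within two strata of equal expected size, residual SD 1.00 after baseline, 10,000 trials per scenario. Two inputs are assumptions because the documents do not give them: R² from 0 to 0.20, and a correlation of 0.5 or 0.7 between stratum and baseline AOU. Ranges below span the two correlations.

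| Assumed R² | SE ratio, formula | SE ratio, simulated | Type I error without / with stratum | Power without / with stratum |
|---|---|---|---|---|
| 0 | 1.000 | 0.995–0.997 | 4.9–5.3% / 5.1% | 77.4–78.5% / 77.3–78.1% |
| 0.02 | 1.010 | 1.006–1.007 | 4.7–5.1% / 4.7–5.2% | 78.7–78.9% / 79.1–79.4% |
| 0.05 | 1.026 | 1.021–1.024 | 4.6–4.8% / 5.0–5.3% | 78.0–78.2% / 79.1–79.5% |
| 0.10 | 1.054 | 1.050–1.053 | 4.1–4.3% / 4.5–4.8% | 78.7–79.1% / 81.4–81.9% |
| 0.20 | 1.118 | 1.114–1.118 | 3.4–3.9% / 4.8–4.9% | 78.4–80.2% / 85.4–86.5% |

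Monte Carlo standard errors are about √(0.05 × 0.95 / 10,000) = 0.2 points for type I error and √(0.8 × 0.2 / 10,000) = 0.4 points for power.

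**Standard error against its own sampling SD.** With the stratum omitted, the ratio of model standard error to empirical SD of the estimate is 0.99–1.00 at R² 0, about 1.04 at 0.10 and 1.07–1.09 at 0.20. This is the source of the conservatism.

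**How much of the stratification gain survives omission.** At R² 0.20 and correlation 0.5, the empirical SD is 0.2477 without the stratum and 0.2393 with it, against 0.2689 when R² is 0 at the same total residual variance. The retained share is (0.2689 − 0.2477) / (0.2689 − 0.2393) = 0.0212 / 0.0296 = 72%. At correlation 0.7 it is (0.2716 − 0.2527) / (0.2716 − 0.2396) = 0.0189 / 0.0320 = 59%.

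**What these R² values mean clinically.** With equal strata and residual SD 1.00, the difference in mean change between strata at the same baseline AOU is 2 × √(R² / (1 − ρ²)), with ρ the assumed correlation. For ρ = 0.5 and 0.7 this is 0.52 and 0.63 points at R² 0.05, 0.73 and 0.89 at 0.10, and 1.03 and 1.25 at 0.20. At R² 0.20 the gap between strata would exceed the 0.75-point treatment effect.

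**The case against.** The strongest reply is that the harm is conditional and may be negligible. Nothing in the documents shows that severity predicts change once baseline AOU is known, and up to R² 0.05 the gain is about one point of power. The Discussion expects recovery to have plateaued, which gives no reason to expect large differences in change between strata among controls. This stands, and it limits the size of the point.

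Some stronger readings are tempting but not supported:

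- *The standard error is definitely overstated.* Only if R² exceeds zero, which the documents do not establish. A scenario such as R² = 0.36 would need a gap between strata of at least 2 × √0.36 = 1.2 points, and nothing in the documents supports that.
- *The benefit of stratifying is thrown away.* Balance between the arms remains, and so does well over half of the precision gain in the R² 0.20 scenario. What is missing is mainly the standard error's recognition of it.
- *The 80% power is undermined.* The sample size takes no credit for stratification. The simulated values of about 78–79% without the stratum reflect the t distribution (78.7%), not the omission.
- *The results would be invalid for every outcome.* The estimate is unbiased and type I error does not rise above nominal. For the FMA-UE outcome, the continuous baseline already carries most of the information in the stratum. Compliance and safety are not analysed by ANCOVA.

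It could also be said that an article condenses a fuller protocol and that an unseen analysis plan may add the stratum. That has limited force. The article is not silent on covariates: it names the one that enters the model, and that choice does not match the allocation scheme.

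**Conclusion.** The mismatch between design and analysis is real, and its direction is known: conservative if severity is prognostic beyond baseline, harmless if not. Over the assumed R² of 0 to 0.20, the cost runs from nothing, through about one power point at 0.05 and 2.7–2.8 points at 0.10, to 6.3–7.0 points at 0.20. These figures rest on 56 evaluable patients, strata of about equal size, residual SD 1.00 and a correlation of 0.5 to 0.7 between stratum and baseline AOU. None of these except the evaluable number and the SD comes from the documents, and the plan's SD is taken here as the SD after baseline adjustment. This is an efficiency improvement of uncertain size. It does not threaten the validity of the trial, but it is worth making because the downside is close to nil.

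**What to change.** In Statistical Analysis, before any unblinded analysis, specify the primary model as an ANCOVA of change in MAL-14 AOU on treatment group, baseline AOU and the randomisation stratum (FMA-UE <32 or ≥32). Use the same structure, for consistency, for the other outcomes analysed by ANCOVA. For the FMA-UE outcome keep the continuous baseline; the stratum adds little there. Fixing this in advance also removes a later choice between results with and without the stratum.

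The cost is one degree of freedom. The stratum is recorded for every patient before allocation, so no further data or patients are needed. If the stratum is not prognostic, simulated power changes by 0.1 to 0.4 points (77.4% to 77.3%, and 78.5% to 78.1%), within simulation error.

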Key elements that characterize effective stroke rehabilitation interventions are intensity of practice, and task- and context-specificity (9, 10). Provision of feedback is another important ingredient for effective motor learning after stroke (11). In the last decade, rehabilitation technology has enabled higher intensity of practice and new methods of feedback. Examples of applied technologies for the upper limb are robotics and virtual reality (12, 13). However, these interventions often lack context-specificity, as the training is almost always performed in a clinic and to date, a beneficial effect on what patients actually do with their paretic upper limb in their daily lives has not been reported. Furthermore, many of these technological developments require a high-financial investment in terms of costs and human resources. Recent developments in the field of tracking and feedback technology have provided low-cost tools (e.g., sensors) that incorporate key elements for effective stroke rehabilitation outside the clinic. These tracking and feedback tools have the potential to motivate patients to use their paretic upper limb in daily life while they are in their home environment. With that, they possibly are able to maintain or even improve gains made during the intensive rehabilitation period and facilitate a translation to the patients’ daily life. These tools most often rely on accelerometer data, which have been found to be reliable and valid in stroke subjects (14, 15), and correlate well with patient-reported upper limb use in daily life as assessed by the Motor Activity Log (16). Previous research has shown that stroke survivors have a high adherence to wearing accelerometer devices at home (17) and report good acceptance levels and high usability scores (18, 19). These tracking devices can be used to give augmented feedback regarding movement outcomes or success rate (i.e., knowledge of results) (20, 21). Knowledge of results is an external form of feedback that can encourage a patient to reach a certain goal, such as using the paretic upper limb at least a pre-defined number of times a day (e.g., 100) when performing daily life activities. In this example, the external feedback given by the trackers could enhance a patient’s intrinsic motivation to improve the number of times he or she uses the upper limb during the day. The provided feedback should be tailored to the individual needs to increase motivation, compliance, and effectiveness. There are various feedback modalities available, such as vibrotactile, visual, and auditory feedback. A recent study reported that stroke patients preferred vibrotactile feedback over visual and auditory feedback (19). However, the application of visual feedback on a smartphone has also been indicated as an effective way of delivering feedback (22). With that, the optimal medium for providing feedback remains unknown.

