### Stepwise Procedures

Subjects will be recruited at three study centers in Switzerland: University Hospital Zurich (academic hospital), cereneo—Center for Neurology and Rehabilitation (rehabilitation clinic), and Zürcher RehaZentrum Wald (rehabilitation clinic) by the local principal or sub-investigator. The participant timeline is displayed in Figure 1. The written participant information and informed consent forms (in German) can be obtained by the corresponding author. After having obtained participant consent, the baseline assessment (T0) will be performed. Randomization will take place after the baseline assessment and depending on the group allocation, participants will be handed over the trial arm-specific devices and receive instructions accordingly. Randomization and device hand-over will be performed by study personnel not involved in assessments (e.g., physical therapist and study nurse). The intervention period has a total duration of 6 weeks. The post-intervention assessment (T1) takes place at day 45 ± 3 after baseline and the follow-up assessment (T2) at day 90 ± 6 after baseline.

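### The planned secondary analysis adjusts the arm effect on MAL-14 AOU for wear compliance, which is measured after randomisation and may itself respond to feedback

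*Protocol article*

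**What the plan says.** All of the following is in the protocol article.

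- **Main model (Statistical Analysis).** "An analysis of covariance will be applied, with the baseline value of the measure of interest as a covariate". The population is all randomised patients: "All randomized subjects will be included in the analyses according to the intention-to-treat approach".
- **Secondary model (same section).** "In a secondary analysis, compliance to wearing the trackers", taken from the sensor data, "will be added as a covariate for analysis of the primary outcome MAL-14 AOU".
- **Compliance as an outcome (same section).** "Compliance to using the devices during the 6-week intervention period and safety data will be presented by trial arm", and it is also compared between groups. Table 1 lists sensor-based compliance among the secondary outcomes.
- **Timing (Stepwise Procedures).** "Randomization will take place after the baseline assessment and depending on the group allocation, participants will be handed over the trial arm-specific devices". Table 1 places the sensor data in the intervention period only.
- **Whether feedback changes compliance.** The Introduction says in general terms: "The provided feedback should be tailored to the individual needs to increase motivation, compliance, and effectiveness". The Discussion states the trial's own expectation: "we do not expect to see a difference between groups regarding safety and compliance to wear the devices".

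**The concern.** Wear compliance arises after allocation, so allocation can influence it. The same section treats it both as an outcome to compare between arms and as a covariate for the arm effect.

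There is a plausible route from allocation to wear. Arm Activities are counted only while the tracker is worn, so daily goals, the progress LEDs and the app game advance only with wear (Experimental Intervention). Controls have vibration and LEDs switched off and no app (Control Intervention). Repeated vibrating reminders could also put some patients off wearing the device, so the direction of any difference is open.

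If wear does differ between arms, conditioning on it causes two problems. It removes whatever part of the effect acts through wearing the device. It also brings in bias from unmeasured causes, such as motivation, that drive both wear and self-reported arm use. Compliance also means different things by arm: wearing an active feedback device, or wearing a silent one. A reader may take the adjusted coefficient as the effect after allowing for adherence, which it does not estimate.

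**Working it through.** **The plan's own figure.** Sample Size gives a difference of 0.75, SD 1.00, two-sided alpha 0.05 and 80% power. The normal approximation is n = 2 × (1.96 + 0.84)² × 1.00² / 0.75² = 27.9, so 28 per group (power 80.1%), as stated. This calculation does not involve compliance and is unaffected.

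**Formula.** For least squares without an arm-by-wear interaction:

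adjusted arm coefficient = unadjusted arm coefficient − (d × s)

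Here d is the arm difference in wear (given baseline MAL-14 AOU), in within-arm SDs. The slope s is that of MAL-14 AOU change on wear within arms, in points per SD. This is algebra and holds whatever the causal structure.

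**Inputs.** Neither d nor s is in the documents. Assumed: d from 0 to 0.75 SD in either direction, s from 0.2 to 0.4. The zero is included because the Discussion expects no difference.

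| size of d | s = 0.2 | s = 0.3 | s = 0.4 |
|---|---|---|---|
| 0 | 0 | 0 | 0 |
| 0.25 | 0.05 | 0.075 | 0.10 |
| 0.50 | 0.10 | 0.15 | 0.20 |
| 0.75 | 0.15 | 0.225 | 0.30 |

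Against 0.75 points, 0.05 is 7%, 0.15 is 20% and 0.30 is 40%. If feedback raises wear, the adjusted effect is too small. If it lowers wear, the adjusted effect is too large.

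**Simulation check.** 28 per arm, true total effect 0.75, within-arm SD 1, 2000 runs per scenario, and no baseline score in either model. Some scenarios include an unmeasured shared cause with correlation 0.5 with wear and an effect of 0.3 on the outcome, which adds 0.5 × 0.3 = 0.15 to s. Cells show the value predicted by the formula, then the simulated mean of the adjusted coefficient.

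| Scenario | s | d = 0.2 | d = 0.5 | d = 0.8 |
|---|---|---|---|---|
| Wear effect 0.3 | 0.30 | 0.69 / 0.68 | 0.60 / 0.59 | 0.51 / 0.51 |
| Wear effect 0.3 and shared cause | 0.45 | 0.66 / 0.66 | 0.525 / 0.53 | 0.39 / 0.39 |
| Wear effect 0.5 | 0.50 | 0.65 / 0.65 | 0.50 / 0.50 | 0.35 / 0.35 |
| Shared cause only | 0.15 | 0.72 / 0.73 | 0.675 / 0.67 | 0.63 / 0.63 |

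At d = 0 the adjusted mean is about 0.75 in every scenario. The model without compliance stays at 0.74 to 0.76 throughout. The last row shows a shift even when wear has no effect on the outcome.

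**The case against.** The strongest defence is that the trial does not plan for wear to differ. The Discussion expects equal wear compliance, both arms receive the same six weekly calls to wear the devices (Additional Information Regarding the Interventions), and the device reminders prompt arm use rather than wear. Compliance is also reported and compared by arm, so readers can check the premise. With equal wear there is no shift, and the covariate may even gain precision: at d = 0 the simulated rejection rate was about 0.78 to 0.79 without compliance and 0.80 to 0.88 with it.

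Much of this stands, and it rules out three stronger readings that a reader might infer.

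- **That the primary result is biased.** It is not. The compliance model is expressly secondary, and the only covariate named for the main ANCOVA is the baseline value.
- **That raising wear is the protocol's stated purpose for feedback.** The Introduction sentence is a general remark on tailoring feedback, and the Discussion says the opposite about this trial. The documents support only that feedback may change wear.
- **That the adjusted effect could change sign.** At the 0.75 target, the largest assumed shift leaves 0.75 − 0.30 = 0.45, and the most extreme simulated scenario leaves about 0.35.

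The defence does not rescue the analysis. Equal wear is an expectation that the trial itself will test. A comparison with 28 patients per arm can miss a modest difference. If the expectation holds, the adjusted coefficient says nothing about adherence that the main model does not.

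**Conclusion.** The point holds for the secondary analysis only. Adjusting the arm effect for wear compliance serves no adherence question: with equal wear it returns the intention-to-treat effect on average, and with unequal wear it returns that effect shifted by −(d × s). Under the assumed ranges the shift is 0 to about 0.30 points in size, up to 40% of the 0.75-point target, in either direction. Both ranges are assumptions, and the true size cannot be derived from the documents. The main intention-to-treat analysis and the sample size stand. This should be changed, but it does not threaten the trial's primary conclusion.

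**What to change.** In Statistical Analysis, remove compliance as a covariate for the between-arm effect on MAL-14 AOU. Keep the planned description and comparison of compliance by arm. Add that the relation of wear time to MAL-14 AOU change will be shown within the experimental arm as a non-randomised, exploratory description.

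If an adherence-adjusted effect is wanted, use an instrumental-variable estimate with randomised arm as the instrument, as a sensitivity analysis only. State the exclusion restriction with it. A wear threshold meets that restriction only approximately, because experimental patients below the cut-off still receive vibration, LED and app feedback. Controls receive no active feedback, so the estimate is roughly the intention-to-treat effect divided by the proportion of experimental patients above the cut-off. It overstates the effect if those below also benefit.

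The cost is about one sentence of wording. Sample size, data collection and the primary analysis do not change. The optional instrumental-variable estimate has a wider confidence interval.
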